#### Phase V: Ethics Sub-Study

The protocol for the ethics sub-study was recently published (52), giving best-practice guidelines for such research worldwide. A separate, optional post-operative ethics sub-study will also be offered. Participants will be informed about this option in the main study PIS. In the main study consent form, they will be asked if they agree to being contacted about the post-operative ethics sub-study.

It will involve one 2.5-hour session with an independent psychiatrist, [name], near the end of the post-operative follow-up period (after 6 months). The sub-study will have a separate PIS and separate informed consent form. This consent form will be requested for the participant’s permission to draw upon the assessment recordings and measures obtained during the main DBS study for use in the subsequent ethical research and analysis.

If the patients wish to be contacted regarding this ethics sub-study, they will be sent the information sheet during the follow-up period. If they consent to participation, the single post-operative interview will occur at the end of the post-operative follow-up period, in order to maintain [name]’s roles as an advocate and a clinical researcher distinct.

The post-operative ethics interview will explore the ethical issues with the participant that surround the research. [name] will elicit her experience of participation, her reflections on this, and also views in hindsight of the ethical issues surrounding the research from the participant.

At the end of the 15-month protocol period, the patient has the option to remove the DBS device which can be done in a simple operation with minimal risks. There will be the option for an annual research follow-up for up to 4 years. At the end of protocol period, or at any point subsequently, the patient has the option to remove the DBS device which can be done in a simple operation with minimal risks. If the participant decides to keep the DBS stimulator *in situ*, they will have routine neurosurgical DBS follow-up every 12 months for clinical care. The annual research follow-up if consented to would take place at the same time and include the following:
The same questionnaires as completed monthly during the main study.The same computerised tasks as completed pre- and post operation.A FaceTime/Skype or phone interview covering psychiatric symptoms and individual experience.The same neuropsychological battery they completed pre-operatively.

## Safety

An SAE is any untoward medical occurrence that results in death, is life-threatening, requires inpatient hospitalisation or prolongation of existing hospitalisation, or results in persistent or significant disability/incapacity.

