Two lines of evidence indicate that DBS might be effective in SE-AN. Firstly, OCD and AN are highly co-morbid, with both disorders showing a high degree of compulsivity (22–24). The second arises from case reports and series. A patient with severe OCD also found improvement in co-morbid anorexia following DBS (25). Further case reports and case series of DBS for SE-AN (26–28) suggest benefit, although none have included double-blind DBS on–off phases. The largest case series, of 6 patients with SE-AN (29) involved DBS applied to the subcallosal cingulate, a neural target previously used for treatment-resistant depression. Regarding safety, the authors initially reported one serious adverse event (SAE): a seizure 2 weeks post-operatively in the context of AN-related metabolic disturbance, with no permanent sequelae. A further patient had a panic attack intraoperatively, and another had an air embolism, but there were no long-lasting adverse effects of the surgery for either participant. A follow-up paper reported sustained symptomatic improvement and weight restoration in three out of six patients, possibly mediated by improvements in mood regulation (30). A recent single case study has also reported improvement in eating disorder psychopathology and mood in an individual with chronic AN, following DBS to the bed nucleus of the stria terminalis (28).

Individuals with AN experience an aberrant sense of reward from weight loss and self-starvation (9, 31, 32) with neural evidence that reward processing becomes abnormal (33, 34). Energy-dense food is anxiety-provoking and aversive, such that individuals become unable to eat to sustain life (35, 36). The compulsive pursuit of self-starvation in AN represents a major barrier to treatability, rendering contemporary treatments highly aversive and contributing to high dropout and relapse rates (31, 37). If these disturbed reward processes could be characterised and subsequently interrupted at a neural level, it would revolutionise the treatment of AN.

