Given the high mortality and morbidity rates of SE-AN (51), additional risks to patients of surgery and entering this study are small, with a potential cost–benefit analysis that justifies ethical equipoise (52). [name], who performs all the DBS operations, has an excellent personal safety record and has performed thousands of operation on patients with Parkinson’s disease. He has also operated on adults with chronic pain and children with movement disorders. The procedure itself has an overall risk of stroke of less than 1%, a haemorrhage-causing death of 0.01% and a risk of wound infection of 5%. To minimise the risk of surgery, the patients will be medically stable prior to surgery. They must have a normal ECG and electrolytes, be free of severe binging or purging or severe depression/suicidality, both of which pose added background risks. The technique (as performed in Oxford) is very well tolerated and can be done in one stage, supported by two to four nights as an inpatient in the neurosurgical ward. DBS has a one-off cost of approximately £40,000 to implant a rechargeable device with a 10-year lifespan. As the mechanisms, efficacy and optimal DBS target for intervention in AN are yet to be established, it should be regarded as an experimental treatment, with the risk that it will not be effective. However, given the extremely poor outcome in terms of morbidity and mortality for those with SE-AN, it is plausibly an intervention where the benefits may outweigh the risks and costs.

A significant body of research suggests that altered reward processing contributes to the maintenance of SE-AN and that this is influenced by higher cognitive control processes (9). We hypothesise that DBS to the NAcc may ameliorate aberrant reward processing and AN psychopathology.

In this clinical trial, our aims are to examine (1) the safety, acceptability and feasibility of DBS to the ALIC at the NAcc in SE-AN; (2) to map neural mechanisms and symptomatic change following DBS; (3) to explore ethical issues, capacity, consent and patients’ views pre- and post DBS and (4) to explore the longer-term effects of DBS in SE-AN.

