#### Phase IV: Post-operative Follow-up Phase

##### Post-operative Assessments, Aiming to Track the Neural and Symptomatic Change As a Result of DBS, Will Involve

*Weekly* Self-report-rating scales of eating disorder psychopathology, anxiety and depression involving the True Colours text-messaging system started in phase I: http://oxtext.psych.ox.ac.uk/true-colours (5 min) (see Phase II: True Colours) (see Figure 1 for more details). Weekly side effects questionnaires, the SAFTEE-SI (81) and DBS side effects questionnaire (82).

Monthly

Interview with [name] and [name]. Repeat of baseline measures collected pre-operatively [see Phase II: Assessment with Research Team (Repeated at All Subsequent Monthly Follow-ups)].Joint neurosurgery–psychiatry reviews with [name] and [name], senior nurse practitioner and [name]. During this review, neurosurgical parameters (such as the degree of stimulation) and psychiatric parameters (such as experience of eating disorder and co-morbid psychiatric symptoms) will be jointly assessed. Any necessary adjustments to stimulator intensity will then be programmed.

Post-operative Neuroimaging

Resting state and food “wanting” task under MEG (13), at OHBA, at month 3 (pre-DBS switch-on), two scans in month 10 in DBS on and off conditions and at the end of study in month 15. Post-operative MRI is not possible with the stimulator implanted for safety reasons.Following each MEG scan, participants will carry out the LOFPQ food reward task. Tasks from the CANTAB (80) and a task measuring habit formation (50) will be carried out twice during the DBS on-off phase and at the end of the study (see Figure 1).

Post-operative neuropsychological assessment at 15 months (12 months after DBS switch-on) will be a repeat of those tests detailed in Section “Phase II: Neuropsychological Assessment.”

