### Data Monitoring

Data monitoring for the project will be conducted by the CI and co-investigators. The study may also be audited by the CTRG. There will be no external monitoring of the study. The project will be under ongoing review for safety and efficacy by the CI and [name]. The study may also be audited by the CTRG, with extensive protocols from the University of Oxford. Any SAE directly relating to the DBS electrode insertion and which cannot be immediately resolved will result in electively stopping the trial prematurely.

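### The printed SAE definition is a closed list with no limb for other medically important events, so some important events would miss expedited reporting and the SAE tally

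*Protocol article*

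**What the plan says.** The Safety section gives a one-sentence definition. An event is serious if it "results in death, is life-threatening, requires inpatient hospitalisation or prolongation of existing hospitalisation, or results in persistent or significant disability/incapacity". That makes four criteria: death, threat to life, inpatient admission or a longer stay, and lasting or significant disability. They are joined by *or*. Nothing marks them as examples, and there is no residual category.

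The label is then used in two places.

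- **Reporting Procedures for SAEs.** An SAE goes to the ethics committee if the chief investigator judges it both related to a research procedure and not listed in the protocol as expected. The report is due within 15 days and is copied to the sponsor.
- **Data Monitoring.** Early stopping of the trial is triggered by "Any SAE directly relating to the DBS electrode insertion and which cannot be immediately resolved". The same section says there is no external monitoring. Ongoing review of safety and efficacy is by the chief investigator and a colleague, and the sponsor's office may audit.

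Safety information is also collected without regard to seriousness. Phase IV (Post-operative Follow-up) has two side-effect questionnaires every week and a monthly joint neurosurgery and psychiatry review at which "psychiatric parameters (such as experience of eating disorder and co-morbid psychiatric symptoms) will be jointly assessed". The first aim, in the Introduction, is to examine "the safety, acceptability and feasibility of DBS to the ALIC at the NAcc in SE-AN"; it is not defined as a count of SAEs.

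**The concern.** In a first study of an implanted brain device in six or fewer patients, some of the events an oversight body would most want to hear about can miss all four criteria. Examples are a brief seizure at home, a suicide attempt that was not life-threatening and was managed without admission, or a lead or wound problem revised without an inpatient stay.

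These are foreseeable events. The Introduction reports that the largest earlier series, also of six patients, recorded as its one SAE "a seizure 2 weeks post-operatively in the context of AN-related metabolic disturbance, with no permanent sequelae". It gives a 5% risk of wound infection for the procedure. It also requires patients to be free of "severe depression/suicidality, both of which pose added background risks" before surgery, which shows that suicidality was recognised as a hazard in this population.

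What is at stake is escalation. An event outside the definition has no stated route to the ethics committee or the sponsor, and no external monitor is described who would pick it up independently. The published SAE tally would omit it too.

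**Working it through.** The article gives no SAE rate or threshold to reproduce, so the main check is to apply the sections to the same events.

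**Step 1. Apply the definition and its consequences.** Each event below is assumed to be non-fatal, not life-threatening, not disabling and managed without admission. If any of these fails, it is already an SAE as printed.

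| Event | SAE as printed | SAE with a medically-important limb | Expedited report if the limb is added | Stopping rule if the limb is added |
|---|---|---|---|---|
| Self-limiting seizure, judged related and not listed as expected | No | Yes | Yes | Not met: it has resolved |
| Suicide attempt | No | Yes | Only if judged related and not listed as expected | Not met on its face: not directly relating to electrode insertion |
| Device, lead or wound event needing surgical revision | No | Yes | Only if not listed as expected; wound infection is a named risk and may count as expected | Met only if it directly relates to insertion and is not immediately resolved |

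The SAE classification changes in all three rows. Expedited reporting changes clearly in the first row and conditionally in the others. The stopping rule is barely touched.

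**Step 2. Show how much one classification can move a tally in six patients.** The input is n = 6, the maximum in Data Analysis. Assume one seizure among six patients, meeting none of the four criteria. The exact (Clopper-Pearson) 95% limits are:

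- Counted, 1/6 = 16.7%. Lower limit 1 − 0.975^(1/6) = 0.4%. The upper limit solves (1 − p)^6 + 6p(1 − p)^5 = 0.025, giving p = 64.1%.
- Not counted, 0/6 = 0%. Upper limit 1 − 0.025^(1/6) = 45.9%.

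The intervals overlap almost wholly. What changes is whether the report shows an event at all.

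**Step 3. Ask how likely an event is that raises the question.** The chance of at least one event in six independent patients is 1 − (1 − p)^6.

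- p = 5%: 1 − 0.95^6 = 26%. This equals the Introduction's figure for wound infection, taken here as a per-patient risk.
- p = 1/6: 67%.
- p = 30%: 88%.

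The last two values of p are assumptions that show a range. None of these results is the chance of a *missed* event, because the article does not say what share of such events would be managed without admission. They are ceilings for that chance at each p.

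**The case against.** The strongest reply is that little would be lost. Several parts of it stand.

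- **Admission is not the only route.** A seizure or suicide attempt that threatens life or leaves disability is an SAE wherever it is managed. The gap is limited to events that miss all four criteria.
- **The safety aim does not rest on the SAE count.** A reader might infer that safety, as the first aim, will be under-counted. The article does not support that. No endpoint is an SAE count, and the weekly questionnaires and monthly reviews can record an event whatever its seriousness.
- **The stopping rule is mostly unaffected**, as the table shows.
- **The earlier series is not a benchmark.** A reader might infer that this trial would look safer than that series through definition alone. No comparison of SAE rates with it is planned; the comparison named in Data Analysis is with the team's own neuroimaging case–control study. The Introduction does not give that series' SAE definition or say whether its seizure led to admission. If it did, the printed definition would capture it.
- **Suicidality is screened.** Current severe major depression is an exclusion, and the selection ranking favours patients without current severe depression or self-harm. This lowers the risk at entry but does not classify an attempt that occurs later.
- **This is an article.** Protocol version 6 is not shown and may carry a further criterion.

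One part does not succeed. Recording an event is not escalating it: nothing in the article links the questionnaires or monthly reviews to ethics committee or sponsor reporting. Nor is this a detail that the article simply leaves out. It prints a complete definition, and its Discussion recommends the protocol as a starting point for future trials.

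**Conclusion.** The point holds as a defect in the definition as printed. Four closed criteria leave some clinically important events outside expedited reporting and outside the SAE tally, in a study without external monitoring. The clearest case is a related and unexpected seizure that is not life-threatening, not disabling and needs no admission.

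The size is modest. One reclassified event is the difference between 1/6 and 0/6 in an SAE table, and that contrast is an illustration which assumes the event meets none of the four criteria. The conclusion does not extend to the safety aim as a whole, and it reaches the stopping rule only for unresolved events directly relating to electrode insertion. It rests on reading the list literally and on version 6 having no further limb. If version 6 has one, the defect lies in the publication and not in the conduct of the trial.

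**What to change.** First check protocol version 6 (11 November 2016). If it already has a limb for other medically important events, correct the printed definition to match.

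If it does not, amend the Safety section by adding: *or is otherwise judged medically important by the investigator (for example seizure, suicide attempt, or a device, lead or wound event needing surgical revision)*.

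Then re-read the recorded events of the five enrolled patients against the extended definition, including their weekly questionnaires and monthly review notes. Report SAEs under both the printed and the extended definition, so that no reclassification looks selective.

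Because the stopping rule is worded in terms of SAEs, the amendment should state how the extended definition bears on it, so that the Safety and Data Monitoring sections agree. How that rule should read is for the investigators and the ethics committee.

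The cost is one clause, a record review for five patients, possibly a few more expedited reports, and an SAE count that may be slightly higher. Assessments and sample size do not change.

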### Reporting Procedures for SAEs

“An SAE occurring to a participant should be reported to the REC that gave a favorable opinion of the study, where in the opinion of the Chief Investigator (CI) the event was: ‘related’ – that is, it resulted from administration of any of the research procedures; and ‘unexpected’ – that is, the type of event is not listed in the protocol as an expected occurrence. Reports of related and unexpected SAEs should be submitted within 15 days of the CI becoming aware of the event, using the NRES report of serious adverse event form (see IRAS/NRES website). All reports will be cc’d to the sponsor Clinical Trials & Research Governance, University of Oxford (CTRG)”.^1^

### Data Analysis

Number of participants: this is an exploratory study of up to six patients, and therefore a precise power calculation is not possible. External review of the protocol for an initial single patient pilot (by the international expert in the neuroscience of AN, [name], University of San Diego) suggested the scientific importance of extending the study to include more patients.

Treatment effects will be established using within-subject analyses comparing baseline characteristics with patient assessment at each monthly follow-up session and by comparing change in symptoms during periods when the stimulator is “on” and periods when the stimulator is “off.” We plan to use multiple regression, analysis of variance and *t*-tests using SPSS software to analyse the data. Results can be compared to our published findings from a linked multimodal neuroimaging case–control study of reward processing in current AN, recovered AN and controls (12, 13, 36).

In addition, MEG data will be analysed using in-house software and open software packages. Preprocessing of data will rely on propriety software supplied by the scanner manufacturer. We will employ both signal and source space methods, building on our previous approach to analysing and interpreting neural data obtained in patients with AN. Non-parametric statistics and general linear modelling will be used to establish significance.

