**Method:**

This is a longitudinal study of six individuals with SE-AN of >7 years. It includes an integrated neuroethical sub-study. DBS will be applied to the NAcc and we will track the mechanisms underpinning AN using magnetoelectroencephalography, neuropsychological and behavioural measures. Serial measures will be taken on each intensively studied patient, pre- and post-DBS system insertion. This will allow elucidation of the processes involved in symptomatic change over a 15-month period, which includes a double-blind crossover phase of stimulator on/off.

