**Discussion:**

Novel, empirical treatments for SE-AN are urgently required due to high morbidity and mortality costs. If feasible and effective, DBS to the NAcc could be game-changing in the management of this condition. A neuroethical gold standard is crucial to optimally underpin such treatment development.

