## Methods

This is a study of DBS targeting the NAcc in up to six patients with SE-AN, using pre- and post-operative repeated measures. To date, five patients have been enrolled in the study.

The study period is 15 months—see Figure 1 for details of study interventions. There will be pre-operative assessments in month 1, the DBS operation in month 2, followed by the DBS switch-on at the end of month 3. DBS dose will be optimised during months 3–6. During month 10 of the study (6 months after switch-on), there will be two double-blinded 2-week periods of DBS on/off as described by Denys et al. (53). At 15 months (12 months after switch-on), there will be final follow-up tests. This study is a quantitative and qualitative investigation of eating disorder and co-morbid pathology, using MEG to image neural processes, and computerised tasks to assess habit formation. There is also a parallel quantitative and qualitative sub-study of ethical issues involved.

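### Uncontrolled change from baseline is said to establish treatment effects alongside the double-blind on/off contrast, with no statement of how the two are read together

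*Protocol article*

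**What the plan says.** One sentence in the Data Analysis section of the protocol article says how efficacy is to be judged: "Treatment effects will be established using within-subject analyses comparing baseline characteristics with patient assessment at each monthly follow-up session and by comparing change in symptoms", continuing with periods in which the stimulator is on and periods in which it is off. Two within-patient contrasts therefore share the verb *established*:

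- (a) baseline against each monthly follow-up;
- (b) stimulator on against stimulator off.

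The section does not say which contrast carries the inference or what is concluded if they disagree. It lists regression, analysis of variance and t-tests without assigning them to either contrast, and gives no significance level.

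Blinding is described for one part of the schedule only. Under Methods, in month 10, "there will be two double-blinded 2-week periods of DBS on/off"; the Abstract describes a 15-month period "which includes a double-blind crossover phase of stimulator on/off". For the monthly visits, Phase IV specifies "Repeat of baseline measures collected pre-operatively" and a joint neurosurgery–psychiatry review covering stimulation parameters and symptoms together, after which: "Any necessary adjustments to stimulator intensity will then be programmed". No control group is described, and no sham period outside month 10.

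The Introduction says that earlier case reports and series suggest benefit, "although none have included double-blind DBS on–off phases".

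**The concern.** The two contrasts answer different questions. Change from baseline mixes any effect of stimulation with surgery, expectation, monthly specialist contact, regression to the mean and the natural course of the illness. The on/off contrast within a blinded phase removes most of these, because they are present in both periods.

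The Patient Selection Process makes non-specific change plausible. Candidates are ranked partly on how strongly they want to recover, which favours expectation effects, and partly on severity, distress and poor functioning, which favours regression to the mean.

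The Introduction treats the absence of blinded on/off phases as a limit of earlier evidence. Yet the analysis sentence lets the same kind of before/after comparison share in establishing an effect. If patients improve from baseline and show little on/off difference, the text does not say how that result is to be read, and the reading can be chosen after the data are seen. The Discussion offers the protocol as a model for later trials, so the ambiguity could be carried forward.

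**Working it through.** **1. A figure to reproduce.** There is none. The article states no significance level, effect size, SD or power.

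**2. The contrasts side by side.**

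| | Baseline vs monthly follow-up | Stimulator on vs off |
|---|---|---|
| Control | none | patient's own other period |
| Blinding described | none | double-blind, month 10 |
| Who sets stimulation | adjusted at the review where symptoms are assessed | two 2-week on/off periods |
| Verb in Data Analysis | established | established |

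That the monthly visits are open-label is an inference: blinding is confined to month 10, and stimulation is adjusted at the monthly reviews. The article does not use the term.

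**3. How often the before/after test is significant when stimulation does nothing.**

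Inputs from the article: n = 6, the maximum; n = 5 is the number enrolled to date. Assumptions: two-sided 5% paired t-test, one outcome, one visit, no dropout, non-specific improvement of d SDs of the paired change.

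Formula: P = P(T > t_c) + P(T < −t_c), where T is noncentral t with n − 1 degrees of freedom and noncentrality d√n. The critical value t_c is 2.571 for n = 6 and 2.776 for n = 5.

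| d | d√6 | P, n = 6 | d√5 | P, n = 5 |
|---|---|---|---|---|
| 0.5 | 1.22 | 0.171 | 1.12 | 0.141 |
| 1.0 | 2.45 | 0.507 | 2.24 | 0.401 |
| 1.5 | 3.67 | 0.833 | 3.35 | 0.711 |

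Under the same assumptions the blinded contrast stays at 0.05 whatever d is, provided there are no carryover or period effects.

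**4. How often the two would disagree.** Treat the contrasts as independent (a further assumption), with no stimulation effect and n = 6. A significant favourable baseline change with a non-significant blinded contrast has probability P(favourable) × 0.95. P(favourable) is 0.169, 0.507 and 0.833, giving about 0.16, 0.48 and 0.79.

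**5. How strong the blinded contrast is.** With n = 6 and a true standardised on/off effect of 0.5, 0.8, 1.0 or 1.5, power is 0.17, 0.36, 0.51 or 0.83. Reaching 80% needs an effect of about 1.43 (about 1.68 with n = 5). The smallest attainable two-sided sign-test p is 2 × 0.5⁶ = 0.031 with six patients and 2 × 0.5⁵ = 0.0625 with five. Disagreement is therefore a realistic outcome even if stimulation does work, which is a further reason to state in advance how it will be read.

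**The case against.** **No either-contrast rule is written.** A reader might infer that either contrast alone suffices, so that an efficacy claim can rest on the before/after change even when the blinded contrast shows nothing. That reading would give a combined false-claim rate of 1 − (1 − P) × 0.95 = 0.21, 0.53 and 0.84 for the three values of d. The text does not support it: the contrasts are joined by *and*, and nothing says one is enough. If both were required, the same inputs give P × 0.05 = 0.009, 0.025 and 0.042, all below nominal. No combined rate can be asserted. Nor can a doubling of the error rate when d = 0: 1 − 0.95² = 0.098 counts both directions, and favourable results alone give 1 − 0.975² = 0.049. This objection stands in full.

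**The blinded contrast does not cleanly isolate stimulation.** Two-week periods after about six months of stimulation measure short-term withdrawal, may carry over, and say little about the longer-term course. This also stands. The contrast can be the main basis for attribution, but a null result cannot be read as no effect.

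**The study is exploratory.** It has at most six patients, and the Abstract seeks feasibility and preliminary efficacy data. The Abstract's closing claim is conditional: "If feasible and effective, DBS to the NAcc could be game-changing in the management of this condition". Long illness duration also makes a large spontaneous improvement less likely, which argues for the lower end of the range of d. All of this lowers the severity. It does not make *established* a fitting verb for an uncontrolled comparison.

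**Ranking of contrasts belongs in the full protocol or analysis plan.** A missing hierarchy alone could be left there. Here the article makes a positive statement that comparison with baseline will establish treatment effects, and that statement is at fault whatever else exists.

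**Conclusion.** The point holds as one of wording and interpretation. Data Analysis names an uncontrolled before/after contrast, with no blinding described, as a means of establishing treatment effects. It places it beside "by comparing change in symptoms during periods when the stimulator is" on or off, without saying how the two are read together. Followed as written, it credits non-specific improvement to stimulation. For six patients, one outcome and one visit, the chance of a significant before/after result with no stimulation effect is about 0.17, 0.51 or 0.83 at d = 0.5, 1.0 or 1.5.

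Those figures rest on an assumed two-sided 5% level and an assumed d, and they describe the before/after test alone. They are not false-claim rates for the trial, because the article states no decision rule from which such a rate could be derived. Severity is modest: worth correcting, but within a study that presents itself as exploratory.

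**What to change.** Reword the sentence in Data Analysis so that:

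1. the double-blind month-10 on-minus-off contrast is the main basis for any statement that stimulation affects symptoms;
2. change from baseline is reported with individual trajectories and confidence intervals, as the observed course after implantation and stimulation, and is not said to establish a treatment effect;
3. if change from baseline is favourable and the blinded contrast is not, the stated conclusion is *improvement observed, not shown to be due to stimulation*;
4. a null blinded contrast is reported as *not demonstrated*, with the short periods, possible carryover and low power named as reasons.

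The cost is wording only: no added patients, visits or measures, and no change to stimulation or its schedule. The downside is that an efficacy claim becomes harder to make, since the contrast carrying it is short and weakly powered.
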